### Study outcomes

The adverse outcomes of interest will be the development of the first event among cardiovascular disease (myocardial infarction, stroke), future hospitalisation (any hospitalisation, diabetes-related and cardiovascular hospitalisation) and death (diabetes-related mortality, cardiovascular mortality and all-cause mortality). Secondary outcome will be future hospitalisation due to hypoglycaemia, a relevant and potentially preventable adverse outcome. The hospitalisation and death outcomes will be identified using the linked HES and ONS mortality data, respectively. Similarly with severity domains, Read codes and ICD-10 codes (available on the ClinicalCodes.org online repository) will be used to identify the outcomes as appropriate.

### Statistical analyses

#### Diabetes severity algorithm

Using annual data bins and grouping diabetes patients in the training data set (include random 80% of the total diabetes cohort) from 1 April to 31 March between 2007 and 2017, the developed diabetes algorithm will grade the severity of T2DM using predefined (sub)domains. Our study period (after 2006) was selected to ensure very high data quality in primary care, while the addition of secondary care data will make our analyses even more robust, in terms of accurately classifying T2DM severity levels.

We will consider two approaches to derive numerical or categorical diabetes severity scores or levels. First, we will use a binary classification (severity indicator: present/absent) within each subdomain and calculate an aggregate score. The second approach, through hierarchical stratification of end organ microvascular and macrovascular complications, will involve increasing weighting within each subdomain, as severity increases where scores of 1, 2 or three on each subdomain will be assigned based on clinical input in terms of severity. Then, regression models, using death (primary outcome) and future hospitalisation (secondary outcome) as dependent variable, will be fitted from which the weights of its estimates will be used to calculate the weights for severity subdomains. The highest possible severity score will be known when the final list of included domains and subdomains is decided. Hierarchical diagrams of the clinical severity of identified diabetes-related complications domains (figure 1), cerebrovascular domains (figure 2) and cardiovascular (figures 3 and 4, online supplementary figures S1 and S2) domains are presented.

**Figure 1 F1:**
[figure not shown]
Severity hierarchy of diabetes-related microvascular complications. CKD, chronic kidney disease; ESRD, end-stage renal disease.

**Figure 2 F2:**
[figure not shown]
Severity hierarchy of cerebrovascular domains. TIA, transient ischaemic attack.

**Figure 3 F3:**
[figure not shown]
Severity hierarchy of coronary and vascular domains. CABG, coronary artery bypass graft; EVAR, endovascular aneurysm repair; HF, heart failure; MI, myocardial infarction; PAD, peripheral arterial disease; PCI, percutaneous coronary intervention; PVD, peripheral vascular disease.

**Figure 4 F4:**
[figure not shown]
Severity hierarchy of cardiovascular disease domains (heart rate, rhythm and conduction). VF, ventricular fibrillation; VT, ventricular tachycardia.

Subdomains with many measurements over time, such as HbA_1c_ levels and BMI, will be modelled as time-varying covariates (alternative models will be considered to account for non-linear changes). Within each time window, the average of these measurements will be used, and we will also use multiple imputation approaches to account for missing data. Provisionally, we will consider using data records within look-back periods between 3 and 5 years. Different look-back windows within this period will be tested to obtain the optimal time window. Descriptive statistics of the study population and the estimated scores will be performed.

#### Severity algorithm validation

When we have developed a first version of the severity score tool, it will be validated statistically by quantifying the association of severity scores to future adverse outcomes. The primary outcome will be developing a cardiovascular event (myocardial infarction, stroke), future hospitalisation and death (diabetes-related mortality, cardiovascular mortality and all-cause mortality). A secondary adverse outcome will be future hospital admission due to hypoglycaemia, a relevant and potentially preventable adverse outcome. Cox proportional hazards (after assessing proportional hazards assumption) and/or competing-risks regressions will be used to perform survival analyses and assess the relationship between the severity score and outcomes controlling for all available patient characteristics (such as age, gender, ethnicity and level of social deprivation). We aim to analyse and assess how severity scores differ across different levels of these variables. As stated earlier, a random 20% of the study cohort (validation data set) will be used to validate the performance of the severity algorithm that was developed in the training data set (80% of the diabetes cohort). Using the calculated subdomains weights (derived by the regression model estimates), Cox regression analysis will be used to validate the developed severity algorithm and we will assess the model performance using relevant measures (such as area under the receiver operating characteristic curve). Using this analysis, we will also test how much the ’sophisticated' full model that includes all relevant severity domains will add in terms of predictive validity of the adverse outcomes over a simpler model that includes demographic data (age, gender and level of social deprivation) alone.

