## Introduction

The worldwide prevalence of diabetes mellitus is increasing with WHO estimating that over 422 million adults had diabetes in 2016 with a growth in the global prevalence from 4.7% in 1980 to 8.5% in 2014.^1 2^ In the UK, the prevalence of type 2 diabetes mellitus (T2DM) has nearly doubled between 2004 and 2014.^3 4^ People with diabetes have a higher risk for morbidity and mortality when compared with individuals without diabetes,^3 5^ and hence the increasing prevalence presents a significant burden on healthcare resources. Diabetes management expenses are estimated to consume up to 11% of the total healthcare budget in the UK and USA.^6 7^ Diabetes is a complex metabolic condition, of an increasing severity,^8 9^ at individually varying levels, and progressive development of vascular complications and end organ damage over time. Diabetes is mainly managed in primary care in the UK,^10^ overall Europe,^11^ USA^12^ and Asia.^13 14^ In the UK, nearly 75% of the diabetes-associated costs relate to management of diabetes-related complications.^6^

The ‘severity’ of clinical conditions can be conceptualised as a progression of the underlying disease process. Increasing disease severity and development of associated complications lead to greater treatment complexity and clinical impact. The severity of chronic conditions, such as diabetes, has not been widely considered despite the clinical relevance and its likely impact on healthcare systems, where few studies have assessed disease severity among patients with T2DM or have quantified temporal trends or scores of severity.^15 16^

Severity scores could be clinically useful, particularly in T2DM; as such, a new summary score could contribute above what existing risk scores offer (eg, moving beyond risk for death) and also be highly relevant for use in six main clinical and research areas: (1) identifying complex patients with a higher need for future care; (2) identifying patients at early stages of disease (benchmarking); (3) providing information that will directly inform clinical care; (4) identifying trajectories in severity over time; (5) supporting research, for example, by serving as an important diabetes-specific covariate to consider in analyses, similarly to the Charlson Comorbidity Index, or as an outcome; and (6) providing data that will inform resource allocation in health systems, such as the National Health Service.

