Here, we describe the conceptual development of a T2DM severity algorithm model, using electronic health records (EHRs) on clinical consultations and treatments. Our aim is to use routinely collected clinical and administrative data to develop a scoring tool which would quantify and grade the severity of T2DM. This model could potentially be used by clinicians to stratify patients based on disease severity and we aim to demonstrate potential advantages over similar risk scores. To validate the algorithm, our secondary aim is to examine the association of severity grades with risk of three main adverse outcomes: cardiovascular disease, hospitalisation and mortality. The developed severity stratification algorithm is anticipated to have direct impact on clinical practice and have wider implications on service planning and policy-making.

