### Prior studies

Currently, there are limited data around validated severity measures that can be used in routine clinical practice managing patients with T2DM. Consequently, we are in parallel finalising a conducted systematic review for clinical-based diabetes severity models which will inform the refinement of this work. Here, we discuss three relevant diabetes severity measures that have been previously reported from countries outside the UK.

In the first study, Gini *et al* categorised the severity of T2DM (n=300) into four levels based on insulin use and the presence of diabetes-related complications (see online supplementary table S3).^15^ A validation study in a random sample of cases was performed by interviewing their GPs. We, however, aim to include more patients with T2DM and consider more clinical data such as other coexisting conditions, non-insulin therapies, statins and ACEIs that have been shown to be associated with reduced risk of adverse outcomes.

In the second study, a diabetes symptom checklist was created to measure the perceived symptom severity and assess the changes over time in 185 patients with T2DM.^16^ The checklist contained 34 items categorised by main clinical symptoms (see online supplementary table S3). The patterns of comorbidities and prescribed treatments were reportedly associated with significant differences in the estimated severity scores.^16^ The sample size was however relatively small and the checklist was based on patients' perception on diabetes symptoms severity.

Third, Young *et al* calculated a Diabetes Complications Severity Index (DCSI) in 4229 patients with type 1 or type 2 diabetes in one US geographic region to examine its association with adverse outcomes (risk of hospitalisation and mortality).^34^ In comparison to using a simple numerical count of complications, DCSI found to be a better tool to predict adverse outcomes. The authors used pharmacy (insulin use only) and laboratory data to compute the severity index and included patients from clinics with largest ethnic diversity (see online supplementary table S3). However, the DCSI missed additional domains such as diabetes duration, hyperlipidaemia and a wider range of diabetes-related and end organ damage manifestations that we aim to assess in addition to hospitalisation and mortality.

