### Importance and the clinical implications of the severity tool

The developed algorithm and severity tool may have significant implications for primary care both in terms of disease management and resource allocation. Ideally, through future work of further validation and assessment of clinical utility, the severity tool will be of practical use in primary care through its implementation in the clinical computing systems used in the UK.^50^ The clinical significance of the developed severity algorithm to primary care is driven by the inclusion of highly relevant clinical domains, such as diabetes-related complications and comorbidities, mapped to routinely collected data.

Additionally, by assessing the longitudinal patterns of severity, the developed tool may be more clinically relevant than the currently used proxy (HbA_1c_), and thus it could be a more reliable indicator in informing practices’ remuneration for diabetes care. Categorising individuals based on their diabetes severity will be relevant for risk stratification (which may enable safer delegation of care within the clinical team), help identify individualised patient risks and will help practitioners triage patients in need of a greater clinical input which informs towards stratified medicine to reduce future life-changing diabetes-related complications. Moreover, the weights of the severity scores may inform future clinical trials as the scoring tool considers a broader range of cardiovascular conditions than in most randomised clinical trials. Given the relatively low rates of cardiovascular outcomes in some trials, identifying patients with diabetes who are at higher risk via our severity algorithm would help to power trials with overall longer-term benefit for patients. Finally, the composite severity score may serve as an important confounding factor in future research, as an example, to match diabetes cases and controls in observational studies and clinical trials.

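### The article aims to show potential advantages over similar risk scores, but the only added-value comparison it states is against age, gender and deprivation, which cannot show a predictive advantage over an existing measure

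*Protocol article*

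**What the plan says.** The last paragraph of the Introduction states that "we aim to demonstrate potential advantages over similar risk scores". Earlier in the same section the rationale is that "a new summary score could contribute above what existing risk scores offer (eg, moving beyond risk for death", followed by six intended uses.

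Under Severity algorithm validation, "a random 20% of the study cohort (validation data set) will be used to validate the performance of the severity algorithm", with performance judged by measures "such as area under the receiver operating characteristic curve". The authors then plan to estimate how much the full model adds to prediction "over a simpler model that includes demographic data (age, gender and level of social deprivation) alone". No other comparator model is stated.

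Prior studies describes three earlier severity measures. Of the DCSI it reports: "In comparison to using a simple numerical count of complications, DCSI found to be a better tool to predict adverse outcomes". It then says: "However, the DCSI missed additional domains such as diabetes duration, hyperlipidaemia", along with a wider range of complications. The section on clinical implications adds that "the developed tool may be more clinically relevant than the currently used proxy (HbA_1c"), because the tool would follow severity over time.

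**The concern.** The aim and the test point at different comparators. The aim concerns scores of the same kind, whereas the stated test concerns demographics. Table 1 offers previous myocardial infarction, stroke, heart failure, end-stage renal disease, dementia and hospital admissions as candidate domains. The outcomes are cardiovascular events, hospitalisation and death, and the subdomain weights are derived by regression on death and hospitalisation. A model carrying that information would be expected to improve on age, gender and deprivation, and so might a much simpler existing index.

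What is at stake is the interpretation of the result. A clear gain over demographics could be read as fulfilling the aim in the Introduction, although the study would hold no estimate of what the new, more complex score adds to a measure that already exists.

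**Working it through.** The article states no discrimination figure, margin or power for this comparison, so there is nothing to reproduce. The check sets the sections side by side and uses one identity.

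**1. Comparator named in the aim and comparator tested**

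| Section | Comparator | Planned test |
|---|---|---|
| Introduction, aim | Similar risk scores | None stated |
| Prior studies | DCSI, criticised for missing domains | None stated |
| Clinical implications | HbA1c as current proxy | None stated (conditional remark) |
| Diabetes severity algorithm | Count score, approach 1 of the new tool | Built, but no head-to-head stated |
| Severity algorithm validation | Age, gender, deprivation | Stated |

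**2. What the stated test can identify.** Let D be the demographic model, E be D plus an existing measure, and N be D plus the new score. Then

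AUC(N) − AUC(D) = [AUC(N) − AUC(E)] + [AUC(E) − AUC(D)].

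The plan estimates only the left-hand side. A predictive advantage over an existing measure is the first bracket on the right, and it cannot be recovered without fitting E.

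**3. Illustration.** The values are assumed and do not come from the article. Take AUC(D) = 0.70 and AUC(N) = 0.76, so the planned result is 0.76 − 0.70 = +0.06.

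| AUC(E) | AUC(N) − AUC(E) | AUC(E) − AUC(D) | Sum |
|---|---|---|---|
| 0.72 | +0.04 | +0.02 | +0.06 |
| 0.76 | 0.00 | +0.06 | +0.06 |
| 0.78 | −0.02 | +0.08 | +0.06 |

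The reported figure is the same in all three rows, while the conclusion about the existing measure runs from better to worse. If the existing measure itself improves on demographics, the gain over demographics overstates the gain over that measure.

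**4. Could a benchmark be run?** HbA1c is a planned subdomain, and a count score is already approach 1. Table 1 cites the DCSI study for microvascular complications, chronic kidney disease stages 3 and 4, myocardial infarction, angina, fibrillation, heart failure, peripheral vascular disease, stroke, hyperosmolar state and ketoacidosis, so many inputs look available. The DCSI scoring rules are not in the article, so exact computability is likely but not shown. The limitations section rules out questionnaire validation and replication in a separate data set. It does not rule out scoring another index in the same data.

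**The case against.** The aim is hedged and is neither the main aim (to develop a grading tool) nor the labelled secondary aim (association of grades with outcomes). The validation plan fits that secondary aim. Some advantages could be shown without comparing discrimination, such as wider domains, use beyond mortality risk, or tracking over time. This stands, and it confines the point to predictive advantage. That is nevertheless the form of added value the validation section chooses to test.

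A reader might infer that the planned comparison is uninformative because it is certain to favour the new tool. The article does not support that. It asks how much is added, which is an estimate of size, and it gives nothing from which a probability of a favourable result could be computed. The final domains are also undecided, and some may be dropped because of treatment feedback.

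A reader might also infer that the article claims to outperform HbA1c. The remark is conditional discussion text about clinical relevance, and the section refers to future validation work. Nor is it right that every simple competitor is absent, since a count score is already to be built.

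Finally, a condensed article may leave its list of benchmark models to a fuller plan that is not shown. That limits what can be said about the study as a whole. It does not remove the mismatch here, because the article names its comparator and that comparator does not serve its stated aim.

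**Conclusion.** The point holds in a limited form. As written, the only stated added-value comparison cannot show a predictive advantage over an existing severity measure, so that part of the Introduction's aim has no analysis behind it. The comparison with demographics is valid for its own narrower question.

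The size cannot be given as a number. It would be the difference between the gain over demographics and the gain over the best existing measure, and the article supplies neither. The conclusion assumes that the advantage sought is at least partly predictive and that no further benchmark is specified in material not shown. It is a recommended improvement rather than a condition for proceeding.

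**What to change.** In the same 20% validation set, for the same outcomes and over the same stated horizon, add each of the following to the same demographic model:

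- (a) HbA1c alone;
- (b) the simple unweighted count already planned as approach 1, or a count of complications;
- (c) the DCSI, or a stated approximation built from the Table 1 subdomains and laboratory data;
- (d) the new score, locked before the validation data are used.

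Report the difference in discrimination for (d) against each of (a), (b) and (c), with paired bootstrap intervals. Keep demographics alone as the reference floor.

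If this is not wanted, narrow the Introduction's aim to added predictive value over demographics. The conditional HbA1c remark can then remain.

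The cost is a few extra models on data largely planned for extraction, plus the work of defining the DCSI approximation. The reported gain will probably be smaller than the gain over demographics.

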#### Longitudinal trends of diabetes severity

In patients newly diagnosed with T2DM, during the study period, we will assess the temporal trends of severity scores over time by calculating the time needed to progress along the quintiles of the severity scale starting from the date or year of diagnosis and identify the predictors to this progression across quintiles.

While the inclusion of some domains such as carotid artery stenting, the use of ACEIs or lipid-regulating drugs, kidney transplantation and laser therapy are clinically relevant and represent markers of greater level of disease severity, they also improve the prognosis (lessen the grade of severity), that is, raising a risk of ‘feedback’. While we will further assess their role, we may have to not include these domains in the modelling at the analysis stage. All statistical analyses will be conducted using Stata Statistical Software for Windows: Release 15 (StataCorp LP, College Station, Texas, USA).

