### Study population

The study cohort will include individuals aged 35 years or over with T2DM (with ≥1 diagnostic code as in (online supplementary table S1) between 1 April 2007 and 31 March 2017. Patients with an ever record of type 1 diabetes (see online supplementary table S2) will be excluded unless they have records of non-insulin anti-diabetic therapies. We chose the study period after 2006 as the quality of CPRD data has improved substantially to adhere with the then introduced important changes to the national incentive scheme The Quality and Outcomes Framework (QOF), an incentivisation programme for all GP surgeries in the UK.^20 21^ QOF exception reporting process allows general practices to exclude patients from indicators or a clinical domain based on discretionary exception codes. However, evidence on the use of exception codes has shown that they are being used appropriately by practices and overall exception rates for diabetes patients are low.^22^

10.1136/bmjopen-2017-020926.supp1Supplementary data

For this cohort construction, we will consider implementing previously validated algorithms designed to identify diabetes cases by avoiding potential misclassification in routinely collected data such as CPRD.^23 24^ Eligible patients will be followed up until censored at the earliest instance of any of the following event dates: patient transferred out of the practice (any cause), last collection date for the practice, the study end on 31 March 2017 or death. The main demographic and clinical characteristics of the defined diabetes cohorts (such as age, gender, geographic region within England, patient-level and general practice-level social deprivation, body mass index (BMI) and baseline glycated haemoglobin (HbA_1c_)) will be identified. Based on our previous studies, the expected sample size in a year will include 11 000 patients with T2DM registered with English general practices linked to the HES Admitted Patient Care data set, HES Outpatient and HES A&E data sets. A random 80% of the identified diabetes cohort (training dataset) will be used to develop the severity tool, with the remaining 20% of the cohort used as a validation data set, as described below.

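### Follow-up is censored at death and the quintile-progression analysis sets no other rule, so a standard time-to-event estimate would overstate how many patients reach each higher severity quintile

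*Protocol article*

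**What the plan says.** Four places in the protocol article bear on this.

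- **Study population.** The rule covers the whole cohort: "Eligible patients will be followed up until censored at the earliest instance of any of the following event dates". The list begins with transfer out of the practice and ends with "last collection date for the practice, the study end on 31 March 2017 or death". Death is not distinguished from the administrative reasons.
- **Longitudinal trends of diabetes severity.** The quantity planned for newly diagnosed patients is "calculating the time needed to progress along the quintiles of the severity scale starting from the date or year of diagnosis". The section also aims to "identify the predictors to this progression across quintiles". It names no estimator or model and gives no rule for patients who die.
- **Diabetes severity algorithm.** The subdomain weights come from "regression models, using death (primary outcome) and future hospitalisation (secondary outcome) as dependent variable".
- **Severity algorithm validation.** This is the only place that mentions competing risks, and there as an option: "Cox proportional hazards (after assessing proportional hazards assumption) and/or competing-risks regressions will be used to perform survival analyses". These analyses relate the score to adverse outcomes. They do not concern movement of the score itself.

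**The concern.** A patient who dies in one quintile can never reach the next. Transfer out, last collection and study end only stop us from seeing progression that may still happen, whereas death makes it impossible. If death is handled like the other three, the estimate describes a population in which nobody dies, and does so correctly only if those who died would otherwise have progressed at the same rate as those who stayed alive. That is hard to defend here, because the score is built so that a higher value goes with a higher risk of death.

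The Introduction lists severity trajectories among the six main uses of the score, and the section on clinical implications suggests that longitudinal severity could inform practice remuneration. Overstated progression would enter both uses, and most strongly where mortality is highest.

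**Working it through.** The protocol states no progression rate, death rate or number of events, so there is no figure of its own to reproduce. What follows is an illustration on assumed rates.

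**Inputs.** From the documents: a study window of 1 April 2007 to 31 March 2017, so at most 10 years of follow-up. Assumed: one upward step, constant and independent hazards, progression λ = 0.05, 0.10 or 0.20 per year, death μ = 0.01, 0.03 or 0.06 per year.

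**Formulas.** Censoring at death (one minus Kaplan-Meier): 1 − exp(−λt). Share who actually progress (cumulative incidence with death competing): λ/(λ+μ) × [1 − exp(−(λ+μ)t)].

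**Example.** λ = 0.10, μ = 0.03, t = 10. Censoring at death: 1 − exp(−1.0) = 63.2%. Cumulative incidence: 0.10/0.13 × [1 − exp(−1.3)] = 0.769 × 0.727 = 56.0%. Gap: 7.3 points before rounding.

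| λ | μ | 10 y, censored | 10 y, cumulative incidence | Gap at 10 y (points) | Gap at 5 y (points) |
|---|---|---|---|---|---|
| 0.05 | 0.01 | 39.3% | 37.6% | 1.7 | 0.5 |
| 0.05 | 0.03 | 39.3% | 34.4% | 4.9 | 1.5 |
| 0.05 | 0.06 | 39.3% | 30.3% | 9.0 | 2.9 |
| 0.10 | 0.01 | 63.2% | 60.6% | 2.6 | 0.9 |
| 0.10 | 0.03 | 63.2% | 56.0% | 7.3 | 2.6 |
| 0.10 | 0.06 | 63.2% | 49.9% | 13.3 | 4.9 |
| 0.20 | 0.01 | 86.5% | 83.6% | 2.9 | 1.3 |
| 0.20 | 0.03 | 86.5% | 78.2% | 8.2 | 3.8 |
| 0.20 | 0.06 | 86.5% | 71.2% | 15.3 | 7.3 |

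**In terms of time.** With λ = 0.10, the censored curve reaches 50% at ln 2/0.10 = 6.9 years whatever the mortality. The cumulative incidence reaches 50% at −ln(1 − 0.5 × 0.13/0.10)/0.13 = 8.1 years for μ = 0.03, and at −ln(1 − 0.5 × 0.16/0.10)/0.16 = 10.1 years for μ = 0.06.

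**If progression and death share causes.** A simulation with a common gamma frailty (200,000 patients, λ = 0.10, the same death hazards, frailty variance 0.5 or 1.0) gave these 10-year results:

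| Frailty variance | μ | No deaths | Censored at death | Cumulative incidence |
|---|---|---|---|---|
| 0.5 | 0.01 | 55.6% | 55.0% | 53.2% |
| 0.5 | 0.06 | 55.4% | 52.0% | 43.2% |
| 1.0 | 0.01 | 50.0% | 49.0% | 47.6% |
| 1.0 | 0.06 | 50.1% | 44.9% | 38.4% |

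The censored estimate now matches neither quantity. It is below the no-death value and above the share who actually progress.

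**Predictors.** A binary predictor was simulated with a hazard ratio of 1.5 for progression and 3 for death (8,000 patients, λ = 0.10). With independent hazards, the Cox ratio censoring at death equals the no-death ratio apart from rounding (1.48 against 1.49, 1.58 against 1.58, 1.46 against 1.47). With frailty variance 1.0 and μ = 0.06 it falls from 1.30 to 1.09. The subdistribution ratio, which reflects the chance of progressing, runs from 1.29 down to 0.87 across the scenarios.

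**The case against.** The strongest reply is that the longitudinal section names no estimator, so nothing says outright that deaths will be censored in that analysis. The Study population sentence describes when record follow-up ends. It cannot be a literal censoring rule everywhere, because death is itself a validation outcome and the dependent variable for the weights. This is a condensed article, and the authors already have competing-risks methods in view. All of this is true, and it makes the application to progression an inference. It is still the natural inference: the rule covers all eligible patients, no exception is made, and the alternative method is attached to other outcomes only.

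A second reply is that the plan targets time and not a 10-year share, and that few newly diagnosed patients can have 10 years of follow-up. The second half stands, which is why the 5-year gaps are shown. The first half does not remove the problem, since the time to a given share shifts as well.

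A reader might go further and infer that the predictors will necessarily be distorted. The documents do not support that. A Cox model censoring at death gives a cause-specific hazard ratio, which is valid as a rate among those still alive. It misleads only if read as an effect on the chance of progressing, or as an effect in the absence of death when the two share unmeasured causes. Older age is a plausible example.

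A reader might also infer that the annual bins hide patients who have a major event and die within one bin. The protocol does not say how a partial final year is scored, so this remains speculation.

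**Conclusion.** The concern holds in a limited form, with moderate confidence. Read as written, the protocol ends follow-up at death and gives the progression analysis no other rule, although death precludes progression and is tied to the score through its weights. A standard estimate on that basis overstates the share who reach each higher quintile. The direction was the same in every scenario tried.

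The size rests on assumed rates. With independent constant hazards over the ranges above, it is about 2 to 15 points at 10 years and about 0.5 to 7 points at 5 years, and small where mortality is low. With shared frailty the gaps tabulated at 10 years run from 1.4 (49.0 − 47.6) to 8.8 points (52.0 − 43.2). For predictors, the conclusion is only that the plan must say which effect is meant.

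**What to change.** Amend the section on longitudinal trends as follows.

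- Treat death as a competing event, or as an absorbing state in a multistate model of quintiles 1 to 5 plus death.
- Report the cumulative incidence of each upward step.
- Report cause-specific predictor effects for progression and for death before progression side by side, and state that they are rates among those alive.
- Keep transfer out, last collection and study end as censoring.

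The cost is a change of wording and a little more analysis. The linked ONS mortality records already supply the dates of death. Reported progression proportions will be somewhat lower.
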